## Abstract

**Background:**

Stroke is one of the major causes of loss of independence, decreased quality of life and mortality among elderly people. About half of the elderly stroke patients discharged after rehabilitation in a nursing home still experience serious impairments in daily functioning one year post stroke, which can lead to difficulties in picking up and managing their social life. The aim of this study is to evaluate the effectiveness and feasibility of a new multidisciplinary transmural rehabilitation programme for older stroke patients.

**Methods:**

A two group multicentre randomised controlled trial is used to evaluate the effects of the rehabilitation programme. The programme consists of three care modules: 1) neurorehabilitation treatment for elderly stroke patients; 2) empowerment training for patient and informal caregiver; and 3) stroke education for patient and informal caregiver. The total programme has a duration of between two and six months, depending on the individual problems of the patient and informal caregiver. The control group receives usual care in the nursing home and after discharge.

Patients aged 65 years and over are eligible for study participation when they are admitted to a geriatric rehabilitation unit in a nursing home due to a recent stroke and are expected to be able to return to their original home environment after discharge. Data are gathered by face-to-face interviews, self-administered questionnaires, focus groups and registration forms. Primary outcomes for patients are activity level after stroke, functional dependence, perceived quality of life and social participation. Outcomes for informal caregivers are perceived care burden, objective care burden, quality of life and perceived health. Outcome measures of the process evaluation are implementation fidelity, programme deliverance and the opinion of the stroke professionals, patients and informal caregivers about the programme. Outcome measures of the economic evaluation are the healthcare utilisation and associated costs. Data are collected at baseline, and after six and 12 months. The first results of the study will be expected in 2014.

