### Outcome measures

#### Effect evaluation

##### Primary outcome measures for patient

An overview of all outcome measurements per time point is presented in Table 2. Primary outcome measures are daily activity measured by means of the Frenchay Activity Index (15-items activity scale) [32], functional dependence measured by means of the Katz-15 (15-items ADL and IADL scale) [33], perceived quality of life measured by means of the Stroke Specific Quality of Life scale (49-items stroke specific quality of life scale) [34] and social participation measured by means of two subscales (autonomy outdoors and social life and relationships) of the Impact on Participation and Autonomy (scale about participation in everyday life) [35].

**Table 2 T2:** Primary and secondary outcome variables of the effect evaluation per time point

**Outcome variables**	**Scale**	**No.****of items**	**T0**	**T1**	**T2**

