***Additional outcome measures***					
Background characteristics patient	-	10/5/5	FI	FI	FI
Background characteristics informal caregiver	-	8/7/7	SQ	SQ	SQ
Cognitive functioning patient	Mini Mental State Examination	12	FI	-	-

T0 = at baseline, T1 = after 6 months, T2 = after 12 months, FI = face-to-face interview, SQ = self-report questionnaire.

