### Sample size calculation

Using data from earlier research based on the Frenchay Activity Index score as primary outcome variable [42], an assumed clinically relevant difference in activity level of two stroke populations is at least 3.5 with a standard deviation of 8.9. Based on a power of 0.8 and an alpha of 0.05, the study would need a sample size of 102 patients in each group. With a drop-out to follow-up estimated at approximately 25%, each group should include 128 participants. In total 256 participants are needed for the study.

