## Discussion

This paper presents the study design of a multicentre randomised controlled trial to evaluate the effects and feasibility of a patient-tailored multidisciplinary rehabilitation programme for elderly stroke patients. The programme aims to improve care for elderly stroke patients who are admitted to a nursing home for neurorehabilitation. This study will provide information about the effectiveness, process and costs of the new multidisciplinary rehabilitation programme and will give insight into how the care of elderly stroke patients might be improved. If this trial shows effectiveness and cost-effectiveness of the rehabilitation programme, the aim is to implement the intervention into the Dutch health care system.

Some methodological and practical limitations concerning the current study exist. However, the presented design is the most feasible method to conduct data to evaluate the effectiveness of the intervention.

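### Four outcomes are primary, but the sample size, alpha and power are set for the Frenchay Activity Index alone

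*Protocol article*

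**What the plan says.** The abstract lists four patient outcomes as primary: "Primary outcomes for patients are activity level after stroke, functional dependence, perceived quality of life and social participation". The Objectives section builds the primary aim on the same four and does not rank them. The section on primary outcome measures repeats the list with instruments. It opens with "Primary outcome measures are daily activity measured by means of the Frenchay Activity Index (15-items activity scale", adds the Katz-15 and the Stroke Specific Quality of Life scale (SS-QoL), and ends with "social participation measured by means of two subscales (autonomy outdoors and social life and relationships) of the Impact on Participation and Autonomy". Table 2 puts all four under the primary heading.

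On timing, the abstract says "Data are collected at baseline, and after six and 12 months", and Table 2 schedules every primary outcome at both follow-ups ("T0 = at baseline, T1 = after 6 months, T2 = after 12 months"). Neither follow-up is singled out.

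The Sample size calculation section uses one outcome only: "Using data from earlier research based on the Frenchay Activity Index score as primary outcome variable". Its inputs are a difference of 3.5, a standard deviation of 8.9, power 0.8 and alpha 0.05, and its result is 102 per group before drop-out.

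The Data analysis section applies multiple regression to primary and secondary outcomes alike. It does not say how the four primary outcomes relate to the FAI-based calculation.

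**The concern.** Alpha and power belong to a stated comparison or set of comparisons. Here they are stated for one comparison, while the primary aim covers four outcomes. A reader of the sample size section would take it that the main conclusion carries a 5% false-positive risk and 80% power. With four equal primary outcomes it cannot carry both. If any one result suffices, the error rate is above 5%. If the error rate is protected by splitting alpha, power is below 80%. If all four must succeed, joint power is below 80%.

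What is at stake is the meaning of a positive trial. The Discussion says: "If this trial shows effectiveness and cost-effectiveness of the rehabilitation programme, the aim is to implement the intervention into the Dutch health care system". Nothing in the article settles how many of the four outcomes, or which, have to show a benefit for the effectiveness part of that condition.

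**Working it through.** **Inputs.** From Sample size calculation: difference 3.5, SD 8.9, alpha 0.05, power 0.80, 102 per group. From the outcome sections: four primary outcomes and two follow-up times. The correlations between test statistics are my assumption, because the article gives none.

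**1. The plan's own figure.** The standardised difference is d = 3.5/8.9 = 0.393. The two-sided normal formula gives

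n = 2 × (1.960 + 0.842)² / 0.393² = 101.5, rounded up to 102 per group.

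This matches. A one-sided alpha would give 80, so the calculation is two-sided. Power at 102 is 80.2% (normal) or 79.8% (t-test). The figure is right for one FAI comparison at the full 0.05.

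**2. Any one of four counts, each tested at 0.05.** With no true effect and independent tests, the chance of at least one significant result is

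1 − 0.95⁴ = 18.5%.

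With equally correlated test statistics (simulation, 1,000,000 draws per row):

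| Assumed correlation | At least one of four below 0.05 |
|---|---|
| 0.3 | 17.4% |
| 0.5 | 15.6% |
| 0.7 | 13.0% |
| 0.9 | 9.3% |

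Counting only results in the programme's favour, independence gives 1 − 0.975⁴ = 9.6%, against a nominal 2.5%. At correlation 0.5 it is 7.8%.

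**3. Alpha split over four.** Bonferroni gives 0.05/4 = 0.0125, with critical value 2.498. The expected FAI test statistic at 102 per group is 0.393 × √(102/2) = 2.81. Power is approximately Φ(2.81 − 2.498) = 62% by the normal formula, and 61% by the t-test. Under Holm, 0.0125 is only the first-step threshold. FAI faces a looser one once another outcome has been rejected, so 61% is a lower bound there. Holding 80% at 0.0125 would take 145 evaluable patients per group.

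**4. All four must succeed.** Alpha then needs no split. If every outcome has the FAI effect size, joint power at 102 per group is 0.802⁴ = 41% under independence, 56% at correlation 0.5 and 62% at correlation 0.7.

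**5. More than four tests.** If the two follow-ups are tested separately, there are 4 × 2 = 8 tests. If the two participation subscales are tested separately as well, there are 5 × 2 = 10. Under independence the any-one rates are 1 − 0.95⁸ = 33.7% and 1 − 0.95¹⁰ = 40.1%. At correlation 0.9 they are 12% and 13%. These are upper counts, since the article does not say that the tests are separated in this way.

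**The case against.** The strongest reply is that this is a condensed article whose analysis plan is not shown. A multiplicity rule, a success criterion and the handling of time are often left to that plan, and the article nowhere says that multiplicity will go unadjusted. That stands, and the absence of such a rule is not the point made here. The point is that the article states both a four-outcome primary aim and a one-outcome alpha and power. A plan that splits alpha makes 102 per group too few for 80% power. A plan that selects FAI alone departs from the abstract, Objectives, outcome section and Table 2. Either way the article's text has to change.

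A second reply is that sizing a trial on one of several primary outcomes is common, and that the singular phrase in the sample size section may describe the earlier study or merely the outcome chosen for the calculation. That is fair. A reader might infer that the article describes two different trials, but this is too strong: the sample size section does not demote the other three outcomes. The calculation still covers FAI only, however the phrase is read.

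A reader might also infer a 40% false-positive risk from ten primary tests. The documents do not support that as the trial's error rate. Testing each time point separately, scoring "two subscales (autonomy outdoors and social life and relationships) of the Impact on Participation and Autonomy" as two outcomes, and applying 0.05 to each test are all inferences. Table 2 lists participation as one 12-item row, and the 0.05 appears only in the sample size section. Independence is also implausible for related scales in the same patients.

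Nor is the rate in step 2 the error rate of the implementation decision, which the Discussion makes depend on cost-effectiveness as well.

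**Conclusion.** The concern holds. The stated alpha of 0.05 and power of 0.80 describe one FAI comparison and not the four-outcome primary aim. Under the any-one-suffices reading, with each outcome tested at 0.05, the false-positive chance is 18.5% under independence and about 17% to 9% for assumed correlations of 0.3 to 0.9. Roughly half of that favours the programme. It rises further if time points or participation subscales are tested separately, which the text leaves open. Under a Bonferroni split, FAI power at 102 evaluable per group is about 61% (a floor under Holm). Under the all-four reading, joint power is about 41% with independence and 56% at correlation 0.5, provided each outcome has the FAI effect size. None of the three readings, in any case computed, delivers both 5% and 80%.

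**What to change.** Before any unblinded analysis, choose one of two routes.

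- **One primary comparison.** Name FAI at one pre-specified time point as the sole primary comparison at two-sided 0.05. The sponsor should choose 6 or 12 months and give the reason. The article's concern with impairment one year after stroke points to 12 months, while a programme lasting two to six months makes 6 months defensible too. The other three outcomes, and FAI at the other time point, become key secondary outcomes under Holm or a fixed order. The 102 evaluable per group then stands as calculated.
- **Four primary outcomes.** Keep all four, name one time point, state Holm across them, say whether participation is one score or two, and restate FAI power as about 61% at the first step. If participation counts as two scores, Holm runs over five and that figure falls further.

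The text changes are small: objectives, outcome section, Table 2, sample size and data analysis. The real cost is that three outcomes lose primary status on the first route, and the stated power falls on the second. The trial is registered and has been recruiting since October 2010, so either route alters the primary endpoint or its stated properties. It must be dated, justified and recorded as an amendment in both the protocol and the registry.

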**Trial registration:**

International Standard Randomised Controlled Trial Register Number ISRCTN62286281, The Dutch Trial Register NTR2412

## Background

Stroke is one of the major causes of loss of independence, decreased quality of life and mortality among elderly people [1,2]. Each year, about 45,000 people in the Netherlands suffer from stroke and associated functional impairments [3]. Almost 56% of stroke patients are 65 years or older [4].

In contrast to other countries, nursing homes in the Netherlands fulfil an important role in the rehabilitation of older stroke patients [5]. In the Netherlands, 31% of stroke patients are admitted to a geriatric rehabilitation unit in a nursing home after hospital discharge [6-8]. Stroke patients in general are admitted to a geriatric rehabilitation unit in a nursing home when they are over 65 years of age and have coexisting multimorbidity, which means that they are incapable of completing an intensive neurorehabilitation programme in a regular rehabilitation centre.

About half of the stroke patients discharged home after rehabilitation in a nursing home still experience serious impairments in daily functioning one year post stroke, that complicate fulfilling their former social roles [9-12]. Common residual problems of elderly stroke patients are emotional and psychological problems such as depression or cognitive deficits, social problems and health-related problems including rest paralysis and fatigue [13-17]. Besides having negative consequences for the patients, these problems may also increase the care burden and decrease the quality of life of their informal caregivers [18].

Currently, in the Netherlands there is a lack of tailor-made, specialised multidisciplinary aftercare following rehabilitation in nursing homes [19]. This may result in inadequate coping skills with the remaining physical, cognitive and/or psychosocial impairments in their home environment [20,21]. These problems may lead to difficulties in the performance of normal day-to-day activities, fulfilling former social roles, maintaining the functional level which has been achieved in the nursing home, and may have negative influence on the burden of care and quality of life of the patient and informal caregiver [22-24]. Eventually, permanent admission to a residential care facility or nursing home could become necessary. However, tailor-made multidisciplinary aftercare may prevent this and contribute to elderly stroke patients living independently in the community as long as possible.

To date, there is no effective aftercare programme available [25]. But research findings in the field of stroke aftercare suggest that adequate aftercare should include, after discharge, follow-up treatment in the patients’ home environment which improves personal independence in daily living [26]. Furthermore, it should include strategies to increase the skills to cope with the remaining physical, cognitive and/or psychosocial impairments, to improve social participation and to maintain functional level after rehabilitation [27]. Support for the informal caregiver is important to decrease the burden of care and improve quality of life.

Based on consideration of shortcomings in current stroke care for older stroke patients and the improvements as suggested in the literature, a multidisciplinary rehabilitation programme for older stroke patients is proposed. This paper presents the design of a multicentre trial evaluating a new multidisciplinary rehabilitation programme for older stroke patients admitted to a geriatric rehabilitation unit of a nursing home.

### Objectives

The primary aim of this study is to evaluate the effect of this new rehabilitation programme on the level of daily activity, functional independence, perceived quality of life and social participation in elderly stroke patients as compared with usual care. In addition, the effect of the programme on the perceived care burden and quality of life of the informal caregiver is assessed.

The aim of the process evaluation is to gain insight into implementation fidelity, programme deliverance and the opinion of the stroke professionals, patients and informal caregivers about the programme. The aim of the economic evaluation is to assess the effects of the programme on health care utilisation and associated costs of elderly stroke patients.

## Methods

### Study design

The design of this study is a multicentre randomised controlled trial with patients allocated to either an intervention or control group. The study design is presented in Figure 1. The study consists of an effect, process and economic evaluation, and will be carried out in the south of the Netherlands. Eight nursing homes with a specialised geriatric rehabilitation unit for stroke patients participated in this study.

**Figure 1 F1:**
[figure not shown]
Design of the study evaluating the multidisciplinary rehabilitation programme.

The study and research protocol have been approved by the medical ethics committee of the university hospital Maastricht and Maastricht University (MUMC+), the Netherlands.

### Study population

The study population consists of stroke patients and their primary informal caregivers. The inclusion of patients starts directly after the acute hospital phase. Patients are eligible to participate in the study when they meet the following inclusion criteria: admission to one of the participating geriatric rehabilitation units due to a recent stroke, aged 65 years or over, living independently in the community before a stroke, expected to be able to return home after discharge and giving informed consent to participate. The multidisciplinary teams of the participating units will check whether patients fulfil the inclusion criteria. The teams usually consist of a nursing home physician, a physiotherapist, an occupational therapist, a speech therapist and a psychologist. If the patient and the informal caregiver are unable to give informed consent, or the patient is medically unstable and not able to start rehabilitation, the patient will be excluded. In addition, for every participating patient his/her primary informal caregiver is invited to participate in the study. A person is considered to be the primary informal caregiver in case the patient indicates him/her as the person mostly involved in informal and social care related activities on a long term basis.

### Randomisation

The randomisation procedure is conducted by a research assistant, who is not involved in the geriatric rehabilitation care. Randomisation is performed based on a computerised block randomisation schedule (block size 8) to allocate eligible patients to the intervention or control group in each of the participating nursing homes. Participants allocated to the intervention group receive the multidisciplinary rehabilitation programme and participants allocated to the control group receive usual care.

### Blinding

The participating nursing homes, patients, informal caregivers and the multidisciplinary teams who are participating in the study are not blinded for the treatment allocation. Research assistants involved in data collection and data analyses are blinded for treatment allocation.

### Intervention

#### Description of the multidisciplinary rehabilitation programme for older stroke patients

##### Organisation

The rehabilitation programme consists of the following three care modules: 1) neurorehabilitation treatment for elderly stroke patients; 2) empowerment training for patient and informal caregiver; and 3) stroke education for patient and informal caregiver. The total programme, including all three modules, has a duration of between two and six months, depending on the individual problems of the patient and informal caregiver.

At the start of the programme an individual treatment plan is made including rehabilitation goals facilitating the transition from in- to outpatient rehabilitation care and to guide further rehabilitation at the patient’s home. The individual patient’s goals will be leading the treatment during both the in-patient and home-based rehabilitation. Rehabilitation goals during the total programme are formulated based on the Goal Attainment Scaling (GAS) method. GAS appeared to be an appropriate method as a guide for rehabilitation treatment for elderly people [28]. Both patient and informal caregiver receive a tailor-made treatment programme to improve their individual level of functioning. To evaluate the treatment progress multidisciplinary team meetings will be organised every four to six weeks in the nursing home. To facilitate optimal communication and information distribution an electronic transmural patient record will be used.

#### The transmural stroke care coordinator

In order to facilitate the continuity of care, in the proposed programme a transmural stroke care coordinator is introduced as a new rehabilitation team member. He/she facilitates the transition of nursing home rehabilitation care services to community care by supporting the collaboration between the multidisciplinary stroke team of the nursing home and the community health services, namely community nurses, paramedical professionals and the general practitioner. After discharge, the coordinator conducts home visits, supports the general practitioner by organising multidisciplinary stroke team meetings and guides the patient and informal care giver in learning to apply self-management principles.

##### Module 1: neurorehabilitation treatment for elderly stroke patients

This module will focus on (re)learning the abilities needed for individual patients to function as independently as possible in their home environment. To optimise recovery, increase independence and check whether patients’ home needs any modification before discharge, an occupational therapist and physical therapist will train the patients during guided home visits in their own home environment when they are still staying in the nursing home [29]. The care within this module is conducted by a multidisciplinary stroke team consisting of nursing home professionals, including a nursing home physician, a physiotherapist, an occupational therapist, a speech therapist, a psychologist and a transmural stroke coordinator. Besides treatment, this part of the programme includes all actions needed to ensure further aftercare, as well as activities to facilitate procedures for necessary home adaptations and assisting devices [30].

